# Using transcranial direct current stimulation to improve outcomes and reduce hip osteoarthritis burden (the STIM HIPS study): A protocol for a randomised, triple blind controlled trial

**DOI:** 10.1016/j.jsampl.2024.100056

**Published:** 2024-04-10

**Keywords:** Hip, Osteoarthritis, Brain stimulation, tDCS, Cortical inhibition

## Abstract

**Background:**

Transcranial direct current stimulation (tDCS), *via* an electrical current being sent through the brains motor cortex, can elicit pain reduction and improved function in people with knee osteoarthritis (OA), compared to a sham. However, it is unknown whether tDCS-induced reductions in pain can be expected in hip OA given differences between hip and knee OA phenotypes.

**Methods:**

Two-armed (*n* ​= ​39 per arm), triple-blind, randomised controlled trial, with an 8-week intervention window and 8-week post-intervention follow-up assessing the efficacy of real anodal tDCS plus exercise versus sham tDCS plus exercise. Primary outcome measure is the International Hip Outcome Tool–33 (iHOT-33).

**Aims:**

The primary objective of this randomised controlled trial is to quantify the effect of tDCS and exercise on pain, disability and quality of life in people with hip OA. Our secondary objectives include: 1) quantifying the influence of motor cortex excitability and conditioned pain modulation on treatment effects, and 2) quantifying the economic cost/benefit of tDCS for improving health-related quality of life in people with hip OA.

**Analysis:**

Data distributions will be examined for each outcome and guide preliminary statistical between group test selections. Repeated mixed effects models will determine between-group differences for the primary outcome (iHOT-33), accounting for relevant confounders (i.e., age; sex; body mass index; radiographic severity) with relevant model assumptions examined. Secondary analysis will determine between-group differences for the other outcomes of interest (cortex excitability and conditioned pain modulation).

**Implications:**

This randomised controlled trial investigates a novel intervention to improve pain, function and quality of life in people with hip OA.

Key points
1.The transcranial direct current stimulation (tDCS) intervention described in this study protocol aims to improve pain and function in people with hip osteoarthritis. tDCS has been demonstrated to reduce pain, and by capitalising on the potential reduction of pain should also enable people to increase their physical activity levels. Providing the benefits of tDCS by relieving pain, plus the associated benefits of increased physical activity.2.Transcranial direct current stimulation (tDCS) is hypothesised to improve hip-related pain and function *via* three mechanisms: 1) directly reducing pain through tDCS application, 2) increased physical activity levels due to reduced pain from tDCS application, and 3) enhanced outcomes from rehabilitation due to additional muscular adaptation by using tDCS to reduce cortical inhibition.

## Background

1

Osteoarthritis (OA) is a worldwide problem [1] affecting more than 3 million Australians. OA causes significant personal burden with higher years lived with disability than type II diabetes, ischaemic heart disease or stroke [2]. OA also has a formidable impact on the workforce (>60,000 Australians with lost productive life years) and economic burden (hip OA replacement costs expected to hit $AUD953 million per annum by 2030) [3]. Hip OA has the largest increase in prevalence (171% from 1990 to 2019), compared to other joints [2]. However, research into the prevention, risk factors and management of hip OA is lacking [4], especially compared to knee OA. One field particularly under-researched in hip OA is neurophysiological drivers and treatments.

The brain acts like a car; an accelerator contracts a muscle, a brake stops it. A recent systematic review showed that individuals with hip and knee OA cannot ‘release the brake’ even when contracting at their fullest (maximal voluntary activation), they are unable to generate what should be maximal force [4]. Thus, large differences are apparent in voluntary activation between people with OA and healthy controls, as well as moderate differences between the symptomatic and asymptomatic limb in people with OA [4]. Furthermore, inhibition of the motor cortex has been associated with worse knee OA pain severity and disability [5]. Pilot studies in knee OA have shown brain stimulation techniques like transcranial direct current stimulation (tDCS) can improve pain, disability and function by up to 60% [6]. However, whilst tDCS produces meaningful improvements in knee OA pain [[6], [7], [8]], the effect of performing tDCS during exercise rehabilitation for hip OA is currently unknown.

A tDCS device sends an electrical current through the brain's motor cortex. This current makes it easier for the brain to drive the muscle to activate (i.e., release the ‘brake’), thus increasing muscle strength [9]. tDCS also influences pain. In controls, in the presence of noxious stimuli (e.g., injury), the body releases natural, endogenous analgesia to reduce sensitivity, termed conditioned pain modulation (CPM) [10]. However, in OA, the pain response is impaired and related to pain pattern as well as severity [11]. tDCS, *via* the electrical current being sent through the brain, can alter the CPM response in knee OA [12] and improve pain, compared to a sham [6]. However, it is unknown whether tDCS-induced reduction in pain can be expected in hip OA when voluntary activation deficits appear to be larger compared with knee OA [4].

### Hypothesis

1.1

tDCS will meaningfully improve pain, disability, and quality of life (QoL) in people with hip OA.

### Objectives

1.2

The primary objective of this randomised controlled trial is to quantify the effect of tDCS and exercise on pain, disability and QoL in people with hip OA. Our secondary objectives include: 1) quantifying the influence of motor cortex excitability and CPM on treatment effects, and 2) quantifying the economic cost/benefit of tDCS for improving health-related QoL in people with hip OA.

## Methods

2

### Study design

2.1

Two-armed, triple-blind, randomised controlled trial, with an 8-week intervention window and 8-week post-intervention follow-up. The study will be reported according to CONSORT guidelines [13], and include an economic analysis and process evaluation.

### Clinical trial registration

2.2

The trial (including statistical plans) has been registered in the Australia New Zealand Clinical Trial Registry (ACTRN12624000129583p) and will be regularly updated.

### Ethical considerations

2.3

Ethical approval has been granted by the Edith Cowan University Human Research Ethics Committee (ID: 2023-04901-[name]) and all participants will provide informed, electronic consent.

### Consumer engagement

2.5

Previous consumer input suggested that non-pharmacological interventions that reduce pain while exercising would be beneficial, and consumers supported the novel use of tDCS. Consumers also highlighted barriers, which informed study design (e.g., >3 in-person tDCS sessions per week was not feasible). A research buddy will be sourced in collaboration with the WA Health Translation Network Community and Consumer Involvement Program to provide input into the project as needed.

### Participants

2.6

Recruitment of 78 consenting, adult participants (39 per arm) with a clinical and radiological diagnosis of hip OA will be undertaken (includes accounting for dropouts). The clinical and radiological diagnosis will be made *via* a Sports and Exercise Physician. The clinical diagnostic criteria include: activity-related hip pain (>3/10) and a positive Flexion Adduction and Internal Rotation (FADDIR) test. Radiological OA will be categorised as a Kellgren Lawrence score of greater than or equal to 2 [14].

Participants will be excluded for: rehabilitation in past 6-months; previous lower-limb surgery; hip joint injection within 3 months; neurological conditions; cardiometabolic conditions that preclude exercise; inability to commit to rehabilitation; specific transcranial magnetic stimulation, tDCS or CPM contraindications (Table 1); inability to understand English; <40 years of age.

**Table 1 tbl1:** Contraindications to transcranial magnetic stimulation, transcranial direct current stimulation and conditioned pain modulation.

Assessment	Exclusion Criteria
Transcranial magnetic stimulation and transcranial direct current stimulation	Pregnancy
	Neurological conditions/illness, including epilepsy/convulsion/seizure
	Vascular, traumatic, tumorous, infectious, or metabolic lesion of the brain, even without history of seizure, and without anticonvulsant medication
	Previous or current implants in their body that may be triggered or heated by an electrical current (e.g. pacemaker, intracranial shunts, artificial cochlea, etc)
	Any mental implanted in their head (e.g. surgical clips, staples, shrapnel)
	Frequent or intense headaches
	Previous brain trauma or neurosurgical intervention
	Serious medical complications (e.g. advanced pulmonary, cardiac, liver or kidney disease)
Conditioned Pain Modulation	Cold urticaria
	Raynaud's phenomenon

### Recruitment

2.7

Participants will be recruited over 14 months, *via* clinical networks, clinical research partners (e.g., orthopaedic clinics), social media (e.g., hip OA groups), and word-of-mouth. The research team have an extensive clinical network and expect recruitment to be highly feasible at 5 participants/month.

### Randomisation and blinding

2.8

Following recruitment, participants will be randomised using a computer-generated randomisation list in RedCap® to one-of-two groups: 1) real anodal tDCS ​+ ​exercise or, 2) sham anodal tDCS ​+ ​exercise. Each tDCS device will be numbered (numbers ranging from 1 to 8 as we have 10 tDCS devices, allowing 2 in reserve if devices are lost/damaged). The study coordinator will program each tDCS device to a real or sham program [1:1 (real:sham)]. Participants will then be randomly allocated *via* the study coordinator to a device and will use this single device during all rehabilitation sessions. Thus, all assessors and clinicians performing assessments and rehabilitation will be blinded.

### Intervention

2.9

[name] will train partner physiotherapists in delivering the tDCS and exercise-based interventions for STIM-Hips. The exercise rehabilitation intervention will be identical between groups and will be reported as per the Consensus on Exercise Reporting Template (CERT) [15] in Table 2. Participants will be provided an 8-week gym membership at the provider physiotherapy clinic. The intervention will involve 8 weeks of physiotherapist-supervised exercise, consisting of three in-person visits/week in which participants receive tDCS during each session. Exercise will be based on templates, sent *via* Physitrack®, however these will be individually adapted as able and progressed when participants can complete the prescribed exercise.

**Table 2 tbl2:** Consensus on exercise reporting template.

Item	Protocol
Detailed description of the type of exercise equipment	The majority of exercises will use body weight resistance, however the following additional equipment will be utilised: knee extension machine, hamstring curl machine, leg press machine, circular TheraBand.
Detailed description of the qualifications, expertise and/or training	All exercises will be prescribed by a qualified physiotherapist, with greater than two years of experience in managing chronic hip pain.
Describe whether exercises are performed individually or in a group	Exercises will be prescribed individually and performed individually, however there may be other rehabilitation patients and clinicians in the rehabilitation gymnasium at the same time.
Describe whether exercises are supervised or unsupervised; how they are delivered	Participants will receive 1:1 supervision by a physiotherapist for one rehabilitation session per fortnight (which will include progressing exercises). All other rehabilitation sessions will be unsupervised.
Detailed description of how adherence to exercise is measured and reported	Attendance at the rehabilitation centre will be recorded *via* private practice standard booking system.
Detailed description of motivation strategies	Participants will receive reminder text messages about physiotherapy consultations.
Detailed description of the decision rule(s) for determining exercise progression	All exercises will be prescribed so they are either pain free or have minimal pain (≤2/10 on a numerical rating scale of pain) when performed. Exercises will be progressed when all sets and repetitions can be performed.
Detailed description of how the exercise program was progressed	Not applicable.
Detailed description of each exercise to enable replication	The exercise progressions will be based on patient function but must include: • A single joint exercise for each of the following muscle groups: lumbar extensors; abdominals; hip extensors; hip flexors, hip abductors; hip adductor; knee flexors; knee extensors; ankle plantar flexors. • A multi joint squat pattern (e.g., squat) and bend pattern (e.g., deadlift) movement. • One balance-based exercise (e.g., star excursion balance).
Detailed description of any home programme component	Not applicable.
Describe whether there are any non-exercise components	The additional intervention is provided below.
Describe the type and number of adverse events that occur during exercise	Adverse events will be reported to all study staff as they occur.
Describe the setting in which the exercises are performed	Exercises will be performed in a physiotherapy rehabilitation gymnasium.
Detailed description of the exercise intervention	Participants will be provided double leg single joint exercises (e.g., double leg bridge), before being progressed to single leg single joint exercises (e.g., single leg bridge) and then more highly loaded single leg single joint exercises (e.g., single leg hip thrust). Sets and repetitions will be based on endurance repetitions (e.g., 3 ​× ​15 reps) and performed three times per week.
Describe whether the exercises are generic (one size fits all) or tailored	Exercises will follow the description above but will be individually tailored to the participant and progressed as able.
Detailed description of how exercises are tailored to the individual	Exercises will be progressed when participants can perform 3 ​× ​15 repetitions or regressed if they are causing pain >2/10.
Describe the decision rule for determining the starting level	All participants will be commenced with double leg single joint exercises and progressed as able.
Describe how adherence or fidelity is assessed/measured	Adherence will be determined as the number of sessions attended across the 8-week intervention divided by the number of prescribed sessions.
Describe the extent to which the intervention was delivered as planned	Not applicable.

The tDCS devices (Brain Premier tDCS E1 Plus) will deliver a weak current [2 milliamps (mA)] from a 35 ​× ​35 ​mm anodal electrode [that increases cortical excitability [16]] on the scalp at the vertex (overlying primary motor cortex of the more symptomatic limb) to a cathodal electrode placed over the deltoid tubercle on the upper arm. The physiotherapist will also train the participant in how to self-perform tDCS on non-supervised days, and will be available to provide assistance if needed during non-supervised sessions. Other than electrical stimulation, real and sham procedures are identical. Real tDCS will be performed at 2 ​mA for 20 ​min whilst completing exercise rehabilitation. Sham tDCS will be applied during exercise with the placebo setting active, ramping to give the sensation of tDCS, then dropping to no output with the screen falsely reporting 2 ​mA of output.

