### Outcome measures

2.10

All baseline assessments will be completed within 7-days prior to commencing the intervention and follow-up will occur as per our assessment schedule (Table 3). Self-reported outcome measures will be recorded *via* RedCap® and will take 20–30 ​min for each participant. Physical assessment measures will be recorded by the principal investigator and research assistant directly into RedCap®. Physical assessments will occur at the Edith Cowan University neurophysiology laboratory, in accordance with existing standard operating procedures, and are expected to take ∼120 ​min.

**Table 3 tbl3:** STIM-Hips study assessment schedule.

	Variable	Weeks			
		0	4	8 (post-intervention)	16
Primary outcome variable	The International Hip Outcome Tool–33	x	x	x	x
Secondary outcome variables	Motor cortex excitability	x		x	
	Voluntary activation	x		x	
	Conditioned pain modulation	x		x	
	EuroQol 5 dimensions	x	x	x	x
Other variables	Demographics	x		x	
	Kellgren Lawrence (KL) Score	x			
	Scoring hip osteoarthritis with MRI (SHOMRI)	x			
	Flare-Osteoarthritis questionnaire	X	X	X	X
	Sit to stand pain	x		x	
	Muscle strength	x		x	
	Medication	x	x	x	x
	Physical activity	x	x	x	x
	Work status	x	x	x	x
	Dietary intake	x			
	Lifestyle Measures	x			
	Psychological Measures	x			
	Adherence	Continual			
	Adverse events	Continual			

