##### Adverse events

2.10.3.11

Adverse events will be directly reported to study staff and recorded with date, time and description of incident/event.

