### Adverse events

2.11

tDCS has an excellent safety profile [32]. tDCS has few adverse events when applied with stimulation parameters in line with published guidelines. Adverse events from tDCS are rare or mild, with mild tingling/itching of the scalp most common [6,7,32].

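### Table 2 sends adverse events to all study staff; read literally this includes the blinded outcome assessors and gives them an avoidable, possible cue to allocation

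*Protocol article*

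**What the plan says.** Three parts of the protocol article bear on this.

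- **Who receives reports.** In Table 2 (section 2.9), the row headed "Describe the type and number of adverse events that occur during exercise" is answered with "Adverse events will be reported to all study staff as they occur". The dedicated entry, section 2.10.3.11, reads "Adverse events will be directly reported to study staff and recorded with date, time and description of incident/event".
- **Who is blinded.** Section 2.8, after describing how the study coordinator programs and allocates the devices, concludes: "Thus, all assessors and clinicians performing assessments and rehabilitation will be blinded". Section 2.10 identifies the assessors: "Physical assessment measures will be recorded by the principal investigator and research assistant directly into RedCap".
- **What an event may look like.** Section 2.9 gives real stimulation "whilst completing exercise rehabilitation", so its side effects arise in the sessions that the Table 2 row covers. Sham is described as "ramping to give the sensation of tDCS, then dropping to no output with the screen falsely reporting 2" mA. Section 2.11 says: "Adverse events from tDCS are rare or mild, with mild tingling/itching of the scalp most common".

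**The concern.** A triple-blind trial normally keeps individual event descriptions away from people who measure outcomes, because side effects are a familiar way to guess treatment. Here the stated rule does the reverse: taken literally, every event reaches every staff member in real time. Real current runs for 20 minutes while sham stops after its ramp, so the nature or timing of a scalp sensation might differ between arms, and the record holds both time and description.

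At stake are the week-8 laboratory measures: cortical excitability by TMS, voluntary activation, conditioned pain modulation from pressure pain thresholds, and muscle strength. These depend on participant effort, on the assessor, or on both. Excitability and conditioned pain modulation are also the two outcomes that section 3.1 names for secondary between-group analysis, and they carry the first secondary objective in section 1.2.

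**Working it through.** The plan gives no figure on this point to reproduce, so the check has two parts: reading the passages together, and asking how strong a cue could be.

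**1. Do the passages conflict?** Table 2 says all staff. Section 2.10.3.11 says study staff without the word all; that is looser but does not narrow the Table 2 rule. The principal investigator and research assistant are study staff, record the physical measures, and are blinded under section 2.8. No passage shown withholds reports from them. Read literally, the two rules pull against each other.

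**2. Which measurements are exposed?** Table 3 schedules the physical measures at weeks 0 and 8 only. Week 0 precedes treatment, so only week 8 can be affected. The iHOT-33 is self-reported through RedCap at weeks 0, 4, 8 and 16, and no assessor scores it.

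**3. How strong is the cue?** Let p_real and p_sham be the proportions of participants with a reported stimulation-related event. The documents give neither, so every pair below is an assumption. With 1:1 allocation, the best possible guess from one participant's report status is correct with probability

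0.5 + |p_real − p_sham| / 2.

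Example, 25% v 10%: 0.5 + 0.15/2 = 57.5%.

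Section 2.8 has 8 numbered devices in use for 78 participants, or 78/8 = 9.75 per device, and each participant keeps one device. If a device keeps its program throughout, and someone can link reports to devices, the best guess about a device with 10 users is correct with probability

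0.5 × Σₖ max{Bin(k; 10, p_real), Bin(k; 10, p_sham)}.

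Example, 5% v 2%, where the best rule is to guess real if there is at least one report: 0.5 × [0.98¹⁰ + (1 − 0.95¹⁰)] = 0.5 × (0.817 + 0.401) = 61%.

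| Assumed rates, real v sham | One participant | Ten pooled by device |
|---|---|---|
| 30% v 30% | 50% | 50% |
| 3% v 2% | 50.5% | 54% |
| 5% v 2% | 51.5% | 61% |
| 15% v 10% | 52.5% | 60% |
| 25% v 10% | 57.5% | 75% |
| 40% v 20% | 60% | 76% |
| 70% v 30% | 70% | 90% |

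Both columns are upper limits for the assumed rates, since they suppose a guesser who knows the true rates in each arm. The pooled column also needs ten completed users of one device and knowledge of each participant's device number. Section 2.10.3.11 does not list the device number in the event record. Assessments take place in the university laboratory, whereas the devices are used at the physiotherapy clinic. Nothing shown gives assessors that link.

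**The case against.** The case against is substantial, and most of it stands as a limit on size.

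- **A report is not an allocation.** The record holds date, time and description. The sham is built to imitate the sensation, and section 2.11 describes events as infrequent or slight. A reader might infer that the rule unblinds the assessors. The documents do not support that: with equal rates there is no cue at all, and with rare events it is slight.
- **Pooling by device.** A reader might take the 75% or 90% figures as the consequence of the reporting rule. They come mainly from device sharing, a separate feature of section 2.8, and from a participant-to-device link that assessors are not shown to hold.
- **The primary outcome.** A reader might infer that physiotherapists who guess the arm could steer exercise at will and so bias the iHOT-33. Table 2 sets criteria: everyone starts on double-leg exercises, progresses on completing 3 × 15 repetitions, and regresses if pain exceeds 2/10. Tailoring exists, but within those limits. Physiotherapists also train participants in tDCS, help in sessions and share each participant's chat group (section 2.12), so they would hear of many events whatever Table 2 said.
- **Safety.** Withholding all events from assessors would have a cost. They record the TMS and conditioned pain modulation measures, Table 1 lists contraindications to both, including seizure and frequent or intense headaches for TMS, and one assessor is the principal investigator. A complete bar would be wrong.
- **Source.** The rule is one row of a reporting template in a condensed article, and routing may be set out more fully elsewhere. But this is a rule the article states, not a detail it leaves out, and it conflicts with section 2.8 as written.

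What the objection does not remove is that nothing shown explains why a laboratory assessor needs every participant's events in real time.

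**Conclusion.** The point holds in a limited form. The Table 2 wording, read literally, sends event descriptions to outcome assessors whom section 2.8 declares blinded. The exposure is avoidable and falls mainly on the principal investigator and research assistant at the week-8 physical assessment. The resulting bias cannot be sized from the documents: it is nil if event reports are alike in both arms and grows with the difference between them. Any effect on the iHOT-33 would be indirect, and the sample size is not touched. This is a cheap improvement in wording and access, not evidence that the blind fails.

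**What to change.** In Table 2, replace all study staff as the recipients with the study coordinator, or a designated safety contact who does no outcome assessment or analysis, plus the treating physiotherapist as far as that participant's safety requires. The coordinator already programs and allocates the devices, so this reveals nothing new. Bring section 2.10.3.11 into line.

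Restrict the RedCap adverse-event form so that assessors do not see individual event descriptions before the participant's last physical assessment, and the biostatistician does not see them before the main analysis is complete. State one exception: information needed for safety, such as fitness for the TMS or conditioned pain modulation tests, is passed on.

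The cost is a changed sentence and an access setting, with no extra participants or procedures. The downside is that the coordinator or safety contact must route events and judge what assessors need to know for safety.
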